## Abstract

**Background:**

Robotic surgery offers many potential benefits for patients. While an increasing number of healthcare providers are purchasing surgical robots, there are reports that the technology is failing to be introduced into routine practice. Additionally, in robotic surgery, the surgeon is physically separated from the patient and the rest of the team, with the potential to negatively impact teamwork in the operating theatre. The aim of this study is to ascertain: how and under what circumstances robotic surgery is effectively introduced into routine practice; and how and under what circumstances robotic surgery impacts teamwork, communication and decision making, and subsequent patient outcomes.

**Methods and design:**

We will undertake a process evaluation alongside a randomised controlled trial comparing laparoscopic and robotic surgery for the curative treatment of rectal cancer. Realist evaluation provides an overall framework for the study. The study will be in three phases. In Phase I, grey literature will be reviewed to identify stakeholders’ theories concerning how robotic surgery becomes embedded into surgical practice and its impacts. These theories will be refined and added to through interviews conducted across English hospitals that are using robotic surgery for rectal cancer resection with staff at different levels of the organisation, along with a review of documentation associated with the introduction of robotic surgery. In Phase II, a multi-site case study will be conducted across four English hospitals to test and refine the candidate theories. Data will be collected using multiple methods: the structured observation tool OTAS (Observational Teamwork Assessment for Surgery); video recordings of operations; ethnographic observation; and interviews. In Phase III, interviews will be conducted at the four case sites with staff representing a range of surgical disciplines, to assess the extent to which the results of Phase II are generalisable and to refine the resulting theories to reflect the experience of a broader range of surgical disciplines. The study will provide (i) guidance to healthcare organisations on factors likely to facilitate successful implementation and integration of robotic surgery, and (ii) guidance on how to ensure effective communication and teamwork when undertaking robotic surgery.

## Background

The past two decades have seen a revolution in general surgical practice. In the 1990s, traditional open surgery was challenged by the introduction of laparoscopic techniques, initially for benign conditions, but later extended to the treatment of cancer. Instead of producing large abdominal wounds, the surgeon is able to perform operations using small ‘key-hole’ incisions, through which cameras and instruments are passed. This effectively removes much of the abdominal access trauma. The clinical benefits were soon realised, including less postoperative pain, shorter hospitalisation, quicker return to normal function, and improved cosmetic effect
[1-3]. However, laparoscopic operations are technically more challenging than open surgery, as a result of the two-dimensional operative image, instrumentation with limited freedom of movement, and lack of tactile feedback. The uptake of laparoscopic surgery has therefore been slow; in 2003, the uptake in colorectal surgery was 5% and had increased to only 40% over the 9 years to 2011
[4], despite being recommended by the National Institute for Health and Care Excellence (NICE) since 2006. Robotic surgery offers to solve some of the limitations of the laparoscopic approach. A surgical cart carries four robotic arms, one of which holds the camera, while the other arms hold a variety of surgical instruments. These robotic arms are controlled by the surgeon remotely. The robot provides a stable camera image with three-dimensional field of view, with instruments that provide increased freedom of movement, and a digital platform that enables intuitive instrument handling, tremor elimination, and motion scaling. This enables the surgeon to achieve greater precision and control and simplifies many of the tasks that are difficult with traditional laparoscopy.

Enthusiasm for robotic surgery is expressed by both clinicians and policy makers
[5-7]. Despite this, the many potential benefits robotic surgery offers for patients are currently not being realised to the full extent because of underuse of surgical robots
[8]. Robotic surgery is a complex intervention, by which we mean that it is an intervention aimed at producing change in the delivery and organisation of healthcare services and which comprises a number of separate components that may act both independently and interdependently
[9,10]. These components are not only technological but also organisational and social, and they can all impact the extent to which the technology is successfully introduced, as well as subsequent process and patient outcomes. The successful performance of a surgical operation is dependent on collaboration amongst staff from different professional groups, including surgeons, anaesthetists, nursing staff, and operating department practitioners (ODPs). There is a complex division of labour that requires the various team members to use their different skills collaboratively to accomplish a single, principal activity
[11]. Reports of the use of robotic surgery suggest that a number of factors are important for successful integration, such as having a highly motivated
[12] and/or dedicated robotic team
[13-15] and additional staff
[16]. Operating theatre (OT) staff consider teamwork skills to be critical for easing the integration of robotic surgery, as is having predefined protocols and explicit communication in the event of deviation from the protocol
[17]. There is also acknowledgement that there is a learning curve for the whole team
[18], not just the surgeon, and that the whole team requires training
[19]. However, such recommendations come from small case series (descriptive non-randomised studies) undertaken in single institutions, typically by dedicated robotic surgery enthusiasts
[3], so that little is known about the contextual factors that are necessary for the successful integration of robotic surgery into healthcare organisations more broadly.

Existing evaluations of robotic surgery also fail to consider the impact of robotic surgery on communication, teamwork, and decision making in the OT. Robotic surgery significantly changes the spatial configuration in the OT, with the surgeon at a distance from the patient and team. The surgeon’s visual attention is focused on the three-dimensional image provided by the robot, inhibiting face-to-face communication during the operative part of the procedure. More generally, the size of the robot introduces physical space constraints, resulting in a new choreography of movement around the patient
[17]. The impact of this change in spatial configuration on communication and teamwork in the OT is not a topic that has been explored in evaluations of robotic surgery, which typically focus on the role of the surgeon
[20]. The spatial configuration of team members and technology in the OT influence the gathering of information that is used to inform decision making
[21,22]. More generally, the spatial configuration of OT teams is not arbitrary but affords particular views of the patient, the rest of the team, and different tools and technologies, with the result that different team members have access to different information to inform their decision making
[23]. The nature of the decision making tasks of the OT team may be impacted with robotic surgery. Surgeons report a sense of both physical and psychological isolation from the patient in robotic surgery, and he/she is more dependent on the rest of the team communicating the status of the patient to maintain situation awareness
[17,24]. Consequently, it has been argued that decision making in robotic surgery is essentially collaborative
[24]. In the event of a complication, more of the burden falls on the rest of the team to respond, increasing the importance of the team having a shared situation awareness of what is happening in the operative field and how far they are through the procedure
[17].

Two small studies have looked specifically at differences in communication between laparoscopic and robotic surgery
[25-27]. Both studies found a significant increase in oral communication between the surgeon and the rest of the team in robotic surgery, particularly in relation to the orientation and localisation of organs and the manipulation of instruments, with the effect found to be more pronounced in teams that have less experience in robotic surgery
[25]. If use of robotic surgery interferes with standard practices of coordination among the OT team, the achievement of seamless, efficient and timely teamwork may be hampered. It is important to understand any change in communication patterns because of the well-documented relationship between communication and patient safety, with failures in communication and teamwork being identified as key factors in adverse events in the OT
[28]. Communication and teamwork around robotic surgery are likely to be influenced by processes associated with the introduction of robotic surgery, such as training and changes in team structure, but equally the integration of robotic surgery in surgical practice may be dependent on the extent to which it is consistent with existing practices for coordination.

For robotic surgery to provide the most benefit for patients, it is first necessary to understand the organisational and social factors that support the successful integration of robotic surgery, by which we mean that it becomes embedded into surgical practice, being used routinely and successfully for surgical operations where it offers advantages to the patient. It is also necessary to understand the impacts of robotic surgery on communication, teamwork, and decision making in the OT and how OT teams manage those impacts.

### Aims and objectives

The aim of this project is to understand how and in what circumstances robotic surgery produces both intended and unintended outcomes. This will be achieved through a realist process evaluation, running alongside an existing randomised controlled trial (RCT) comparing laparoscopic and robotic rectal cancer surgery for the curative treatment of rectal cancer. The study has the following research objectives:

1. To contribute to the interpretation and reporting of the trial results by investigating how variations in implementation of robotic surgery, and the context in which robotic surgery is implemented, impact on outcomes such as operation duration, conversion to open surgery, and complications;

2. To produce actionable guidance for healthcare organisations on factors likely to facilitate successful implementation and integration of robotic surgery; and

3. To produce actionable guidance for OT teams on how to ensure effective communication and teamwork when undertaking robotic surgery.

## Methods and design

### Overall design

We will undertake a realist process evaluation that will run alongside ROLARR (RObotic versus LAparoscopic Resection for Rectal Cancer), an international, multicentre prospective, randomised, controlled, unblended parallel-group trial, where the primary outcome is conversion to open surgery (as an indicator of technical difficulty)
[29]. Process evaluations are predominantly qualitative studies that are typically undertaken alongside a trial, but may be undertaken in preparation for a trial or after a trial
[30], and explore how the intervention is implemented
[31]. This involves defining the active components of the intervention and investigating contextual factors that affect its implementation.

Realist evaluation is increasingly popular as a method for evaluating the implementation of complex interventions in healthcare
[32-36] and has been applied in a variety of fields within health systems research
[37]. It does not employ particular methods of data collection but offers a framework for understanding for whom and in what circumstances complex interventions work. It involves building, testing and refining the underlying assumptions or theories of how the intervention is supposed to work
[38]. Realist evaluation can complement RCTs in a number of ways
[39]. Previously, it has been used in preparation for an RCT, to develop hypotheses that were then tested in the trial
[40,41], and for a process evaluation following an RCT, to understand the results of the trial, in terms of how and why the outcomes were achieved
[42,43].

### Phase I. Formulation of CMO configurations

The unit of analysis in realist evaluation is not the intervention but the theories concerning the mechanisms through which the intervention produces certain outcomes in particular contexts. A first task is to identify these theories. In Phase I, the first ‘theory elicitation’ stage of a realist synthesis will be undertaken to catalogue stakeholders’ theories concerning how robotic surgery becomes embedded into surgical practice and its impacts. Such theories are to be found in guidance documentation (*e.g.*, for robotic surgery), position papers, professional journals such as the ‘Health Service Journal’ and the ‘Nursing Times,’ publications of the Royal Colleges, blogs, thought pieces, advocacy pieces, and critical pieces, and so the review will focus on this grey literature. The output of the review will be a series of candidate theories in the form of Context-Mechanism-Outcome (CMO) configurations.

Telephone interviews will be conducted with staff in National Health Service (NHS) hospital Trusts (providers) in England that are using robotic surgery for rectal cancer resection. This will include Trusts that are participating in the trial and those that are not. Interviews will be semi-structured and conducted using the ‘teacher learner cycle’
[44]. Here, the interviewer describes, through their interview questions, the candidate theories to the interviewee, who is then invited to comment, expand and discuss the theories based on their experience of the intervention. Through this process, the interviewer channels the interviewee’s responses to the task of developing and refining the theories. The interviewer proceeds to formalise the interviewee’s theories, based on the information they have given, and the interviewee is then invited to comment on that formalisation. Consequently, the interview is a vehicle for enabling key participants to revise and expand the theory and generate new theories. It is essential that the study captures the perspectives of all professional groups that may influence the effectiveness of the introduction of robotic surgery
[24]. Interviews will first be held with one of the surgeons in each Trust and, through them, we will identify other members of the OT team to interview (surgeons, anaesthetists, theatre nurses, ODPs, trainee surgeons) as well as hospital administrators and managers who were involved in the introduction of robotic surgery into the Trust. All interviews will be audio recorded and transcribed verbatim.

An iterative approach to data collection and analysis will be taken in this phase, to support the gathering of further data on emergent themes. Interview transcripts will be entered into a qualitative software programme (NVivo 10) for indexing. Thematic analysis will be used to analyse the data
[45]. Following the realist strategy, indexing of the data will focus on identifying interviewees’ accounts of how outcome patterns are formed by mechanisms and contexts
[43]. In addition, codes developed inductively will be used to index the data. Similarities and differences in the stakeholder theories will be identified and used to further refine the emerging CMO configurations. Key CMO configurations will then be selected for empirical testing in Phase II.

### Phase II. Empirical testing of CMO configurations

Four case sites will be selected, three of which will be participants in the ROLARR trial and one which is not (on the basis that only looking at sites in the trial would limit the generalisability of the findings, as sites in the trial could be considered to have successfully embedded robotic surgery into their practice). Case sites will be purposively sampled to ensure variation in the contextual factors identified as being significant in Phase I of the research. These are likely to include: process through which the technology was introduced (organisation led vs. clinician led); level of experience with robotic surgery; and whether dedicated robotic teams are employed.

In realist evaluation, a mixture of qualitative and quantitative methods is important to gather data on the mechanisms and contexts of an intervention as well as its impacts
[46]. Data will be collected using a range of methods, which are flexible enough to allow exploration of a variety of CMO configurations. However, the data collection protocol will be revised and further specified at the end of Phase I in light of the theories to be tested.

### Data collection

#### Structured observation

Teamwork during operations will be assessed using OTAS (Observational Teamwork Assessment for Surgery)
[47]. OTAS comprises ratings on five team behaviour constructs: (i) Communication; (ii) Coordination; (iii) Cooperation and back up behaviour; (iv) Leadership; and (v) Team monitoring and situation awareness. These behaviours are assessed during observation of the surgery, with each behaviour scored on a 7-point scale. OTAS distinguishes between different subteams in the OT (surgeons, anaesthetists, and nurses) and different phases of a procedure (pre-, intra-, and post-operative). For one operation, a total of 45 behavioural ratings are generated (5 behaviour constructs × 3 subteams × 3 phases). Researchers will also record additional information for each operation, such as the team composition, each team member’s level of experience of robotic surgery, duration of each phase of the operation, and whether there was a conversion to open surgery.

#### Video

To facilitate a close consideration of robotic surgery in use, all operations that are observed will be video recorded. Video recording has been highlighted as an important tool for understanding safety in the OT
[48] and has been used successfully in a number of studies concerned with the impact of communication and teamwork on surgical performance
[49-51]. The use of two video cameras will allow for the capture of the surgeon’s perspective on the surgical scene and the wider conduct of OT team members.

#### Ethnographic observation

Ethnography has been argued as an essential approach for studying the introduction of technology into healthcare settings
[52]. It is an important complement to the structured observations, allowing unanticipated yet significant behaviours and interactions that fall outside the scope of the observation tool to be recorded in the researcher’s field notes. In addition, ethnographic observation is important for getting a sense of how what happens in the OT fits within the broader context of work and for capturing those aspects of the context that cannot easily be measured, such as the culture of an organisation. Following in the ethnographic tradition, the researchers will, at least in the early stages of the study, keep the scope of the notes wide on the basis that what previously seemed insignificant may come to take on new meaning in light of subsequent events
[53] and should give special attention to the indigenous meanings and concerns of the people studied
[54]. In addition, the researchers will record incidents of observer effects (*e.g.*, participants asking ‘What are you writing?’) to allow analysis of whether participants’ awareness of the researchers’ presence changed over time
[55]. Field notes will be written up as soon after data collection as possible.

### Interviews

Interviews will be semi-structured and will seek to gather data on those outcomes that cannot easily be gathered by other means, particularly those relating to the perceptions of members of the OT team (*e.g.*, level of enthusiasm for robotic surgery, perceptions of teamwork, and perceptions of robotic surgery as an opportunity for training). In addition, due to the infrequency of such events, we are unlikely to see many conversions to open surgery or complications (conversion to open surgery is expected to occur in less than 5% of operations), so we will gather OT team members’ accounts of the reasons for such conversions. All interviews will be audio recorded and transcribed verbatim.

### Data analysis

As in Phase I, an iterative approach to data collection and analysis will be taken. The overall approach to analysis will involve initial comparisons in the processes and outcomes of interest (*i.e.*, those specified in the CMO configurations) between laparoscopic and robotic surgery, before using the data from the robotic surgery operations to test the CMO configurations. We will try to draw on multiple sources of data to test each configuration. Thus, it is through testing the CMO configurations that the various sources of data will be integrated. Table 
1 provides some example theories, based on our current understanding of the literature, and indicates what data could be used for testing each theory.

**Table 1 T1:** Example theories presented as CMO configurations, with data to support testing

**Context**	**+**	**Mechanism**	**=**	**Outcome pattern**	**Data**
Experienced teams	+	Knowledge of how to overcome difficulties in set-up and positioning of the robot	=	Easier access to patient; Reduced operation duration; Reduced conversion to open surgery/complications	Video recordings, operation duration, interviews
Whole OT team involved in implementation	+	OT team perceive benefits for patients	=	Increased motivation among team members to work together to develop solutions to problems	Video recordings, OTAS, interviews
Physical separation between surgeon and OT team	+	OT team less aware of surgeon’s actions	=	Reduced coordination; Increased operation duration	OTAS, video recordings, operation duration
Dedicated robotic teams	+	Develop strategies to deal with physical separation	=	Effective coordination, teamwork, communication; Reduced operation duration	OTAS, video recordings, operation duration
Surgical trainee as part of team	+	Physical separation and different views of operative field makes it harder for surgeon to explain what is happening and monitor trainee’s understanding	=	Reduced satisfaction amongst surgeon and trainee in robotic surgery as opportunity for training	Video recordings, interviews
More experienced teams	+	Understand need to support surgeon’s situation awareness	=	Increased verbal communication of patient state to surgeon; Increased situation awareness of surgeon	Video recordings, OTAS

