### OTAS

Initial analysis of OTAS scores will use a mixed model analysis of variance (ANOVA), with case site and sub-team as between-subjects factors and surgery type (laparoscopic vs. robotic), phase, and behaviour as within-subjects factors
[47]. We will then test the CMO configurations. For example, this could involve checking for a difference in the overall OTAS score in those case sites where the OT team had been involved in implementation compared to those case sites where they were not involved.

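### The Phase II laparoscopic-robotic comparison does not separate ROLARR-allocated operations from others, so the pooled contrast is open to within-site selection of approach

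*Protocol article*

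**What the plan says.** The section on Phase II sets the sites: "Four case sites will be selected, three of which will be participants in the ROLARR trial and one which is not". The stated reason for the fourth site is generalisability.

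The Data analysis section gives the order of work. It begins: "The overall approach to analysis will involve initial comparisons in the processes and outcomes of interest". The comparisons are "between laparoscopic and robotic surgery, before using the data from the robotic surgery operations to test the CMO configurations". Nothing there distinguishes operations whose approach ROLARR allocated from operations whose approach was settled in some other way.

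The OTAS section specifies an initial mixed-model ANOVA "with case site and sub-team as between-subjects factors and surgery type (laparoscopic vs. robotic), phase, and behaviour as within-subjects factors". It names no other factor.

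Under Structured observation, researchers also record each team member's "level of experience of robotic surgery, duration of each phase of the operation", team composition and any conversion. Allocation status is not among the items named.

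**The concern.** ROLARR randomises patients to laparoscopic or robotic surgery. Among operations it allocated, the two groups should differ in case mix only by chance. That protection does not extend to operations it did not allocate. If easier or harder cases tend to receive the robot at the non-trial site, the laparoscopic-robotic difference there mixes the effect of the approach with the difference between cases, and pooling carries part of it into the overall contrast.

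The stake is the first item under Aims and objectives: helping to interpret and report the trial's results, with operation duration among the outcomes named. The Discussion repeats that the study should help explain any longer duration of robotic operations. A Phase II difference that mixes randomised and other operations could be read as an explanation of a randomised result when part of it reflects who received which approach.

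**Working it through.** **No figure to reproduce.** The article gives no number of operations, power, significance level, effect size or SD for Phase II. The check is a reading of the sections together, followed by an illustration on assumed inputs.

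**Reading the sections together**
1. One of four sites is outside ROLARR, so none of its operations is ROLARR-allocated (Phase II section).
2. The article does not say that operations observed at the three trial sites are limited to randomised ones. If they are not, non-allocated operations arise there as well.
3. The comparison is by surgery type, with no subset by allocation (Data analysis).
4. The OTAS factors are case site, sub-team, surgery type, phase and behaviour. None carries allocation status or case mix.

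**What a site term does.** In an additive model with surgery type and site, the pooled contrast is a weighted mean of the within-site contrasts d_s:

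pooled = Σ w_s d_s / Σ w_s, with w_s = n_s p_s (1 − p_s),

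where n_s is the number of operations and p_s the robotic share at site s. Differences in level between sites cancel. A selection shift δ inside d_4 does not; it enters at the weight of site 4.

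- Equal n_s and p_s = 0.5 everywhere (assumed): weight of site 4 = 0.25 / (4 × 0.25) = 0.25.
- Equal n_s and p_4 = 0.8 (assumed): 0.8 × 0.2 = 0.16, so weight = 0.16 / (3 × 0.25 + 0.16) = 0.176.

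| Assumed δ at site 4 (OTAS points) | Pooled bias, weight 0.25 | Pooled bias, weight 0.176 |
|---|---|---|
| 0 | 0 | 0 |
| 0.25 | 0.0625 | 0.044 |
| 0.5 | 0.125 | 0.088 |
| 1.0 | 0.25 | 0.176 |

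**Simulation check (all inputs assumed).** There were four sites of 200 operations, 400 repetitions, a true effect of 0, a residual SD of 0.7 OTAS points, and a 0.5-point difference in level at site 4. Approach was randomised at three sites. At site 4 it depended on a covariate standing for case ease or experience, with log-odds of 0 to 2 per SD, and that covariate moved the score by 0.25 or 0.5 points per SD. The model was additive with one score per operation, so it simplifies the planned ANOVA.

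- With no selection and 80% robotic use at site 4, the bias was 0.119 without a site term and 0.003 to 0.004 with it. The site term does its job on level differences.
- With selection, surgery type plus site left a bias of 0.02 to 0.15; site 4 alone gave 0.12 to 0.63.
- The three randomised sites alone gave a bias no larger than 0.01 in absolute value.
- Adding the covariate also brought the bias to about 0, but only because the covariate was assumed to capture all of the selection.

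The formula agrees with the simulation. For example, a site-4 contrast of 0.226 at 80% robotic use gives 0.226 × 0.176 = 0.040, and the simulated pooled bias was 0.040.

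**The case against.** The case for leaving the plan alone has real weight.

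- **The comparison is preliminary.** It is called initial and precedes the theory testing, which uses the robotic operations. No objective is to estimate a robotic effect on OTAS. The Discussion also plans to combine Phase I implementation data with ROLARR's own outcome data. This stands and lowers the priority. OTAS scores and the phase durations recorded by the observers, however, come from Phase II.
- **The fourth site is deliberate.** It was added for generalisability. This stands, and it is a reason to keep the site in the theory testing. It does not require its operations to be merged into the contrast between approaches.
- **A site-by-type term, natural in such an ANOVA, would reveal a divergent fourth site.** The article does not state one. If fitted, it would show divergence without telling selection from a genuine difference in context.
- **An article condenses a fuller protocol, and data collection is to be revised after Phase I.** Allocation status may therefore be recorded somewhere not shown. The article does fix the list of model factors, and its deferral concerns data collection, not analysis.

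Some stronger readings are tempting. A reader might infer that staff at the fourth site choose the approach by patient or robot availability; the article does not say how it is decided there. A reader might conclude that the effect is confounded; the text supports only that it is open to confounding.

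A reader might also hold that team experience must enter the model. The Background reports more communication in robotic surgery, "with the effect found to be more pronounced in teams that have less experience in robotic surgery". That is effect modification, and omitting a modifier does not by itself bias the average contrast. Experience is also partly a component of how robotic surgery is delivered, and the theories in Table 1 already use it as a context.

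Finally, a reader might suppose that ROLARR-allocated operations give a contrast free of all confounding. Randomising patients balances case mix, not teams. Where dedicated robotic teams exist, team and surgery type stay entangled even at trial sites.

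**Conclusion.** The point holds as a cheap improvement. The planned contrast mixes operations that ROLARR allocated with operations that it did not, and the specified site factor cannot remove selection of approach within a site. That follows from the article's own text on sites, comparison and model.

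No direction or magnitude of bias can be derived from the documents. The figures above show only how a shift would pass through: about a quarter of its value with equal site weights, nothing if there is no selection, and more if non-allocated operations with a similar shift are also observed at the trial sites. They rest on assumed site weights, robotic shares and selection strengths.

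**What to change.** 1. Record for each observed operation whether ROLARR allocated its approach.
2. Report the laparoscopic-robotic contrast for OTAS and operation duration in ROLARR-allocated operations, grouped as randomised, so that conversions stay in their arm.
3. Report the non-allocated operations separately, from the fourth site and any from the other three, and label that estimate observational.
4. Keep all four sites in the testing of the CMO configurations.
5. State that randomising patients does not balance team composition where dedicated robotic teams exist. Describe recorded team robotic experience by surgery type as a supplementary analysis, not as a required model term.

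The cost is one field on the observation form and a few sentences of analysis text. The downside is precision. If the sites contribute equally and every trial-site operation is ROLARR-allocated (both assumed), the main contrast uses three quarters of the operations and its standard error grows by a factor of about √(4/3) = 1.155. The loss is larger if non-trial operations are also observed at those sites. Because the article gives no number of operations, the absolute loss cannot be stated.
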